### The Lake Louise consensus scoring system and high-altitude de-acclimatization syndrome score

2.8.

The Lake Louise consensus scoring system 2018 version will be used to assess the presence of AMS at high altitudes according to the four main symptoms: headache, gastrointestinal symptoms, fatigue/weakness, and dizziness/vertigo. Scores of 0, 1, 2, and 3 correspond to none, mild, moderate, and severe degrees for each symptom, respectively. AMS is diagnosed as a total score of ≥3, combined with headache (1). We will collect this information every day through self-administered questionnaires at high altitudes.

The HADAS will be evaluated according to the scoring criteria for syndromes, which include complaining of dizziness, fatigue, weakness, headache, blurred vision, lethargy, insomnia, dreaminess, difficulty concentrating, memory loss, slow reaction, and physical signs, including chest tightness, cyanosis, palpitation, slow pulse, precordial pain, changes in blood pressure, decreased appetite, changes in body mass, abdominal distension, diarrhea, edema, constipation, cough, asthma, hair loss, sexual dysfunction, tooth loss, numbness of hands and feet, and skin hemorrhagic spots or ecchymosis (2). In addition, these symptoms do not improve under short-term rehabilitation after organic diseases of the heart, lungs, kidneys, and other organs are ruled out. Physicians who have been systematically trained will score the presence of three or more of the above symptoms or signs according to the following criteria: (1) have a slight reaction but not affect daily work for 0 points; (2) affect work but the symptoms improve soon after rest for score 1; (3) seriously affect daily work and symptoms improve significantly after drug treatment for score 2; (4) seriously affect daily work and symptoms do not improve significantly after drug treatment for score 3.

### Respiratory function assessment

2.9.

Participants will be notified in advance to avoid smoking and consuming caffeinated or heavy meals for at least 2 h before the tests. It will be ensured that the indoor environment is suitable for the entire measurement process [in a dedicated temperature-controlled (20–25°C) laboratory]. Lung function will be assessed using the spiroergometry system with Breath-by-Breath technology (Metalyzer 3B, Cortex, Germany, 2022). Standardized assessments of resting lung function will be performed before respiratory tests during exercises. The best attained values of three attempts of forced expiratory volume in one second (FEV1) and forced vital capacity will be recorded. Before each test, the volume sensor will be calibrated using a standard three-liter syringe, and the gas analyzer will be adjusted with two-point calibration using air and a 16.5% O_2_:CO_2_ mixture. Participants will be provided with a fitting face mask, and volumetric and gas-exchange data will be directly transferred to the metabolic cart software (MetaSoft® Studio, Cortex Biophysik GmbH, 2022), with real-time viewing capacity. Maximum voluntary ventilation (MVV) will be measured from a 12-s maneuver of deep and rapid breathing as the corresponding minute volume. Standards for the performance and interpretation of spirometry data will be obtained from the European Respiratory Society and the American Thoracic Society (42).

### Cardiopulmonary exercise test

2.10.

Before CPET, standardized assessments of resting lung function will be performed. Whole tests will be conducted in a dedicated temperature-controlled (20–25°C) laboratory by a physician and a skilled technician, who is blinded to other procedures and details of this study. The baseline physiological measures for all devices used in this study will be measured for 5 min in a resting state and subsequently in a standing position. CPET will be performed in an erect position through an electronically braked cycle ergometer (EC3000e, Customed, Germany) with Breath-by-Breath technology (Metalyzer 3B, Cortex, Germany, 2022). The cycle ergometry exercise protocol comprises four stages of exercise: 3 min of rest, 3 min of unloaded exercise, a continual increase in resistance of 25 W/min, and recovery with 3 min of unloaded cycling. All patients will continue CPET until the development of limiting symptoms such as angina, dyspnea, or muscular fatigue. CPET will be terminated at the discretion of the operating physician if pre-specified termination criteria develop, such as hemodynamic abnormalities, heart rhythm abnormalities, or neurological impairment.

The AT time is estimated from breath-by-breath data using the V-slope method and validated with other plots using the ventilatory-equivalent method and the respiratory exchange ratio method (31, 43). The parameters for AT will be obtained at this time point. Other peak values will be calculated at identical time points. The calculation method for each indicator detected using the metabolic cart software (MetaSoft® Studio, Cortex Biophysik GmbH, 2022) is described in detail in Table 5.

Standard 12-lead electrocardiogram, blood pressure, and SpO_2_ will be obtained throughout the procedure using a 12-lead connection (Custo-Cardio 3000BT-A, Cortex, Germany, 2022) in real-time, blood pressure cuffs (Suntech Tango M2, Cortex, Germany) in the upper arm and a portable finger clip oximeter (Nonin wristOx2 3150, Nonin, United States), respectively. All these parameters of CPET are the direct output from the cardiopulmonary exercise testing system.

### Data collection, management, and analysis

2.11.

#### Data collection and management

2.11.1.

The data collection tools of this study include oral inquiry, questionnaire, laboratory examination report, and export of cardiopulmonary exercise test report. We have collected relevant information about the participants, including socio-demographic characteristics such as age, sex, alcohol use, tobacco use, medical history, nature and duration of illness, etc. The data, including all primary and secondary outcomes collected at Chongqing Xinqiao Hospital and Shigatse Branch Hospital, will be organized in an Excel spreadsheet in the proper format by a trained research assistant. All the data collected will be stored in Human Plateau Resources Biobank at Chongqing Xinqiao Hospital after being checked by the principal investigator and may only be consulted with the permission of the principal investigator. All personal data will be legitimately stored in encrypted folders and kept unavailable to any third party without the consent of the participants in advance. The data sets generated and/or analyzed during the current study are available from the corresponding author upon reasonable request.

#### Statistical considerations

2.11.2.

Continuous variables will be expressed as means ± standard deviations (SD) or as median (interquartile spacing), and categorical variables as *n* (%) according to the Shapiro–Wilk test. Generalized estimating equations (GEE) with an exchangeable working correlation will be employed. Treatment, altitude, and the treatment multiplied by altitude interaction will be considered independent variables under mixed models. At each altitude, a comparative analysis will be carried out between two groups (ubiquinol group and placebo group), and the least significant difference method will be performed to adjust within-altitude differences for multiple comparisons. Correlation analyses will be performed using Pearson correlation for continuous variables, and Spearman Rank tests will be used between categorical variables. In addition, subgroups will be defined by age for analysis since it is known that ubiquinol levels decrease with age (23). Two-sided tests with *p*-values less than 0.05 will be considered statistically significant. IBM SPSS Statistics software for Windows (version 26, IBM, Armonk, NY, United States) will be used for statistical analyses.

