### Setting

2.1.

This is a single-center, randomized, double-blind, placebo-control clinical trial conducted at Chongqing Xinqiao Hospital and Shigatse Branch Hospital [The Shigatse CARdiorespiratory Fitness (SCARF) Study] in 2022 and registered at www.chictr.org.cn (ChiCTR2200059900 and ChiCTR2200066328). The primary hypothesis of this study is that ubiquinol supplementation may improve cardiorespiratory fitness both at high-altitude acclimatization and de-acclimatization, while AMS and HADAS are secondary endpoints. The study complies with the SPIRIT 2013 recommendations (Standard Protocol Items: Recommendations for International Trials) (24) (Supplementary Material S1). Table 1 depicts the overall schedule and time commitment for trial participants.

**Table 1 T1:** Study schedule and time commitment.

Timepoint	Study period					
	Enrolment	Allocation	Post-allocation			Close-out
	−14 days	0	11 days	17 days	28 days	6 months
Enrolment						
Eligibility screen	X					
Informed consent	X					
Medical and travel history	X					
Vital signs	X					
Allocation/randomization		X				
Interventions						
Ubiquinol group						
Placebo group						
Assessments						
Baseline variables: age, sex, height, weight			X			
Outcome variables						
CPET			X	X	X	X
Blood routine examination			X	X	X	
Serum marker examination			X	X	X	
The Lake Louise 2018 score assessment				X		
High altitude de-acclimatization syndrome assessment					X	X

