### Sample size

2.3.

The G-power tool (version 3.1.9.2, Germany, 2017) was used to calculate the sample size by prior power analysis and to estimate all statistically significant results. The *α* error probability was set at 0.05, and the power (1 − *β*) was set at 0.9. With a correlation among repeated measures of 0.5, a sample size of 39 was determined to be necessary to assess the effects of ubiquinol. A sample size of 36 within two groups (ubiquinol group and placebo group) and within-between interactions were calculated with a nonsphericity correction (*ε*) of 1. Considering a 5% dropout rate, based on a sample size of 39, 41 participants would be required finally.

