Peak oxygen consumption (VO_2_)	“Gold standard” assessment of cardiorespiratory fitness.	The VO_2_ value of plateau attained when there is no further (or relatively small) increases in VO_2_ despite further increases in work rate is determined as VO_2_max (28). Consequently, peak VO_2_ is often used as an estimate for VO_2_max. For practical purposes, VO_2_max and peak VO_2_ are used interchangeably. Symptom limitation during an incremental exercise protocol could be taken to reflect the maximal VO_2_ value even though a plateau in VO_2_ fails to appear (29).
% predicted peak VO_2_	Comparison of peak VO_2_ achieved with predicted value for age, sex, and body size.	Using the Wasserman and Hansen formula (30).
VO_2_ at the anaerobic threshold (AT)	Anaerobic threshold refers to the critical point at which muscle metabolism transitions from aerobic to anaerobic metabolism in an incremental exercise test.	Measurement of VO_2_ and VCO_2_, with AT estimated as the breakpoint in the VCO_2_-VO_2_ relationship using the V-slope method (31).
Peak O_2_ pulse	Reflects stroke volume and peripheral O_2_ extraction. Indicates the peak capacity for oxygen extraction on each heart beat.	Peak VO_2_/peak heart rate.
Metabolic equivalents (METS)	The ratio of exercise metabolic rate to resting metabolic rate. Expresses the relative energy metabolism level of various activities based on energy consumption in quiet and sitting positions (32). 1 Met is defined as the consumption of 3.5 ml of oxygen per kilogram of body weight per minute (33).	VO_2_/3.5 ml/min/kg.
% maximum predicted heart rate	Heart rate response to exercise.	Peak heart rate as a percentage of the predicted peak heart rate calculated using the Tanaka formula (peak heart rate = 208–0.7*age) (34).
Rate pressure product (RPP)	Represents the relative level of myocardial oxygen consumption.	The product of heart rate and systolic blood pressure.
VE/VCO_2_ slope	Determined by the dead space fraction of the breath (VD/VT) and arterial PCO_2_. Typically taken to reflect the degree of match between alveolar ventilation and pulmonary perfusion.	Slope of the regression line of VE vs. VCO_2_ (35).
Oxygen uptake efficiency slope (OUES)	Reflects VO_2_ kinetics.	Slope of the regression line of VO_2_ vs. log_10_ VE (35).
VO_2_/work rate slope	Reflects the metabolic cost of performing external work.	Slope of the regression line of VO_2_ vs. work rate.

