Cardiorespiratory fitness reflects the comprehensive ability of the body to transport and utilize oxygen and embodies the overall function of the respiratory and cardiovascular systems (49, 50). VO_2_max is the gold standard for assessing cardiorespiratory fitness and an independent predictor of cardiovascular events and mortality (51–53). Previous studies have indicated that VO_2_max decreases linearly by approximately 8% for every 1,000 m of additional elevation above 700 m, while it descends in an accelerated curve over 6,300 m, suggesting that cardiorespiratory function is impaired at high altitudes (54). However, there is limited information on cardiorespiratory fitness changes during de-acclimatization from a high altitude in healthy individuals, and the underlying mechanisms remain to be elucidated. Thus, in this study, we try to illuminate the possible mechanism by circulating markers of metabolism and the autonomic nervous system (55).

This study has some limitations. First, although this is not a small clinical trial in the CPET trial at a high altitude, this study is limited by a small sample size (*n* = 41) and short follow-up (on days 17 and 28, respectively). Therefore, it is troublesome to implement hierarchical analysis, and these preliminary results need to be confirmed in a large cohort. Second, long-term follow-up may be more meaningful in evaluating ubiquinol supplements on cardiorespiratory fitness.

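### Section 2.11.2 names both GEE and mixed models for the same terms in a 41-participant trial; if uncorrected GEE is what is run, the nominal 5% tests operate at about 6 to 9%

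*Protocol article*

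**What the plan says.** Section 2.11.2 (Statistical considerations) states "Generalized estimating equations (GEE) with an exchangeable working correlation will be employed". The sentence after it lists treatment, altitude and treatment by altitude as the independent variables, and puts them under mixed models. Between-group comparisons are then planned at each altitude. The threshold is "Two-sided tests with *p*-values less than 0.05 will be considered statistically significant". No variance estimator, reference distribution or small-sample adjustment is named.

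The trial is small by its own account. Section 2.3 arrives at 41 participants, section 2.4.1 allocates them 1:1, and the Discussion says "this study is limited by a small sample size".

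On covariates, the schedule in section 2.1 (Table 1) has a row "Baseline variables: age, sex, height, weight". Table 5 describes percent predicted peak VO2 as "Comparison of peak VO_2_ achieved with predicted value for age, sex, and body size". The listed model terms include none of these variables. Section 2.11.2 uses age only to define subgroups.

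**The concern.** GEE and a mixed model are not two names for one analysis. GEE usually draws its standard errors from the sandwich estimator with a normal or chi-square reference, which is justified when there are many independent clusters. Here the clusters are participants, about 20 per arm. The sandwich variance is biased downward at that size, and the large-sample reference ignores the uncertainty in the variance. A mixed model with adjusted degrees of freedom does not have this problem. A reader cannot tell from section 2.11.2 which p-values and intervals the trial will report.

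The sample size in section 2.3 is built on within-between interactions with a nonsphericity correction, which is a repeated-measures ANOVA calculation with a finite-sample F reference. An uncorrected GEE test would depart from that basis.

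A smaller matter is precision. Age, sex and body size plausibly explain part of the variation in peak VO2 between people. The first exercise test is on day 11, after allocation and on treatment, so there is no pre-treatment test result to adjust for. Demographic covariates are the natural substitute.

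**Working it through.** **The plan's own figure.** Section 2.3 states "error probability was set at 0.05, and the power" at 0.9, and then "With a correlation among repeated measures of 0.5, a sample size of 39 was determined to be necessary", with 5% dropout. 39 × 1.05 = 40.95, which rounds up to 41; 39 / 0.95 = 41.05, which rounds up to 42. So 41 reproduces to within one participant. The other figure, "A sample size of 36 within two groups (ubiquinol group and placebo group", reproduces for the interaction if one assumes f = 0.25 and three measurements (power 0.906). No effect size is stated, so f is an assumption. Either way there are about 20 per arm.

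**Type I error of uncorrected GEE.** Inputs: n = 20 per arm, two-sided 5%, complete data, treatment by visit saturated. In this case the GEE estimates are cell means and the sandwich uses divisor n in place of n − 1. The robust Wald statistic is therefore W = T² × n/(n − 1), where T² is Hotelling's two-sample statistic. W is referred to chi-square with q degrees of freedom. Its true distribution follows from F = T² × (38 − q + 1)/(38 q) on q and 39 − q degrees of freedom.

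| Test | q | Chi-square cut-off | T² = cut-off × 19/20 | F | True size |
|---|---|---|---|---|---|
| Group contrast at one visit | 1 | 3.841 | 3.649 | 3.649 on 1, 38 | 6.4% |
| Interaction, 3 visits | 2 | 5.991 | 5.692 | 2.771 on 2, 37 | 7.6% |
| Interaction, 4 visits | 3 | 7.815 | 7.424 | 2.344 on 3, 36 | 8.9% |

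Simulation with arms of 20/21, 19/20 and 18/18 gave 6.2 to 6.5%, 7.4 to 7.8% and 8.9 to 9.5% for the three rows. The interaction results were essentially the same for within-person correlations of 0.5 and 0.8. A fitted GEE (5,000 replicates, 20/21, three visits) gave 5.9 to 6.5% per visit and 7.0% for the interaction. With n − 1 variances and the F reference, the interaction tests returned to 4.9 to 5.1%.

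**Interval width.** The ratio to the exact interval is (1.960 / 2.024) × √(19/20) = 0.944, so the intervals are about 6% too narrow. Simulated coverage was 93.5 to 93.8%.

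**Model-based variance instead.** The only error left is the normal reference: P(|t| > 1.960) on 38 degrees of freedom = 5.7%.

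**Value of covariates at one visit.** Inputs: 20 and 19 participants; R² of 0.3 to 0.5 assumed, because the documents give none. Unadjusted noncentrality is d × √(20 × 19/39) = 3.121 d on 37 degrees of freedom. With four covariates it is 3.121 d / √(1 − R²) / √(36/32) on 33 degrees of freedom. The factor 36/32 is the expected cost of chance imbalance.

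| Difference | Unadjusted | R² = 0 | R² = 0.3 | R² = 0.5 |
|---|---|---|---|---|
| 0.5 SD: noncentrality | 1.561 | 1.471 | 1.759 | 2.081 |
| 0.5 SD: power | 33% | 30% | 40% | 52% |
| 0.8 SD: noncentrality | 2.497 | 2.354 | 2.814 | 3.330 |
| 0.8 SD: power | 68% | 63% | 78% | 90% |

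For the treatment by visit interaction with complete data the gain is zero, because time-constant main effects cancel from within-person contrasts.

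**The case against.** The strongest reply is that the inflation rests on an option the article never states. This is a condensed publication, and the variance estimator and any correction are normally fixed in the analysis plan, which is not shown. If the mixed model is what is fitted, with adjusted degrees of freedom, there is no inflation. That stands. A reader might infer that the trial's tests will run at 6 to 9%, but the documents support this only as a conditional statement.

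The upper figures also need altitude to be coded as three or four visits. The text describes two altitudes, 300 m and 3,900 m. A two-level factor has a one-degree-of-freedom interaction and an error of about 6.4%. That stands too.

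Three other inferences are tempting and go too far:

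- **Leaving out covariates is an error.** It does not bias a randomised comparison. Percent predicted peak VO2 is already standardised for age, sex and size, metabolic equivalents are per kilogram, and percent maximum predicted heart rate is age-based. Nor are these the only prognostic values free of treatment influence: vital signs are taken before allocation, and tobacco use, alcohol use and medical history are collected.
- **GEE fails because participants ill at altitude will miss the exercise test.** No passage says so. The only figure given is 5% dropout.
- **GEE should be abandoned throughout.** A linear mixed model does not suit the binary diagnosis of acute mountain sickness in section 2.8.

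What the reply does not remove is the conflict itself. An analysis plan can choose one of the two model classes, but it cannot make both sentences describe the same fit.

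**Conclusion.** The point holds in a limited form. Section 2.11.2 names two model classes for the same terms, and the passages must be reconciled. The consequence is modest and depends on the choice made: about 6.4%, 7.6% or 8.9% in place of 5% under an uncorrected sandwich variance with a chi-square reference, about 5.7% under a model-based variance, and close to 5% with finite-sample inference. The figures assume complete data and about 20 per arm, and the two higher ones assume that altitude is analysed as three or four visits.

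The covariate point is a suggestion for better precision, not a fault in the plan. Its size rests wholly on an assumed R². It applies to the single-visit group comparisons and costs a little power if R² is near zero.

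**What to change.** State one model for the continuous exercise-test outcomes: a linear mixed model with treatment, visit and treatment by visit, fitted by REML, with Kenward-Roger or Satterthwaite degrees of freedom. Name visit in place of altitude, since days 11 and 28 are both at low altitude and a two-level altitude factor would merge them. If GEE is kept, for example for the binary mountain sickness diagnosis, specify a small-sample-corrected variance with a t or F reference.

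As an optional improvement, prespecify age, sex and body size as covariates for outcomes not already standardised for them. Use values recorded before treatment; Table 1 as printed marks height and weight at day 11, so the source of the weight value needs confirming. Do not adjust for the day-11 exercise test, which is on treatment.

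The cost is wording and syntax, up to four degrees of freedom for covariates, and slightly larger p-values wherever uncorrected GEE would have been too optimistic. No new data are needed.

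### The least significant difference method is described as a multiplicity adjustment but makes none, so the per-altitude p-values will be nominal

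*Protocol article*

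**What the plan says.** Section 2.11.2 (Statistical considerations) plans generalized estimating equations. On the model terms it says: "Treatment, altitude, and the treatment multiplied by altitude interaction will be considered independent variables under mixed models". It continues: "At each altitude, a comparative analysis will be carried out between two groups", namely ubiquinol and placebo, and adds that "the least significant difference method will be performed to adjust within-altitude differences for multiple comparisons". The only significance rule is two-sided, with p-"values less than 0.05 will be considered statistically significant". The section gives no overall test that must be passed first, no division of alpha and no testing order.

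Section 2.5 (Outcomes) defines the primary outcome as cardiorespiratory fitness and lists 14 CPET parameters (my count) to be collected at four visits. Table 1 places CPET on days 11, 17 and 28 and at 6 months. Section 2.3 (Sample size) also works at an undivided level: the alpha "error probability was set at 0.05".

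**The concern.** LSD is a set of ordinary pairwise tests that share a pooled error term, each at the nominal level. It offers some protection in its gated (Fisher) form, where pairwise tests follow only a significant overall test. That protection is complete only for three means of one variable. No gate is stated here.

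The sentence therefore credits the method with a property it lacks. This is a wrong statement in the article, not a detail left to a fuller document. If it is carried into the results paper, nominal p-values will be presented as multiplicity-adjusted. Readers would then discount an isolated positive result too little, in a trial of 41 people with many measures under one primary heading. Treatment estimates are not affected. What is affected is how the p-values are described and interpreted.

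**Working it through.** **Inputs.**
- Per-test alpha of 0.05, two-sided (section 2.11.2).
- Correlation between repeated measures of 0.5: "With a correlation among repeated measures of 0.5, a sample size of 39 was determined to be necessary" (section 2.3). A value of 0.8 is my assumption, to show the effect of closer correlation.
- Total 41 with 1:1 allocation (sections 2.3 and 2.4.1), taken as 20 and 21.
- Number of visits in the family: not fixed by the article, so two (days 17 and 28), three (adding day 11) and four (adding 6 months) are shown. Each visit is treated as one level at which the groups are compared.

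**The plan's own figure.** The point rests on no stated figure except the 0.05. For completeness, 39 × 1.05 = 40.95, which gives the stated 41. The 36 for the interaction is reproduced if an effect size f = 0.25 and three measurements are assumed (power 0.906). The article states neither value. The 39 could not be reproduced with any variant tried, and nothing below depends on it.

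**Step 1: what LSD does within one altitude.** With g groups there are g(g − 1)/2 pairwise contrasts. With g = 2 that is 2 × 1/2 = 1. One contrast tested at 0.05 has a false-positive rate of 5%, with or without LSD, and the LSD p-value equals the ordinary one.

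**Step 2: error across visits, one variable.** If the visits were independent, the chance of at least one false positive in k tests is 1 − 0.95^k:
- k = 2: 1 − 0.9025 = 9.8%
- k = 3: 1 − 0.8574 = 14.3%
- k = 4: 1 − 0.8145 = 18.5%

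Repeated measures are correlated, so the rates are lower. Simulated two-sided t tests at each visit, with no true difference at any visit, give:

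| Visits | Correlation 0.8 | Correlation 0.5 |
|---|---|---|
| 2 | 7.7% | 9.0% |
| 3 | 9.9% | 12.9% |
| 4 | 11.5% | 15.6% |

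Repeat runs differ by a few tenths of a percentage point. Relative to 5%, the range is 7.7/5 = 1.5 to 15.6/5 = 3.1. With Bonferroni, or Holm (which has the same first step), the rate is 3.1–4.7%.

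**Step 3: error across parameters.** Adjusting over visits separately for each variable does not deal with the 14 parameters. If these were independent and each were held at 5%, the chance of at least one false positive would be 1 − 0.95^14 = 51%. CPET parameters are correlated, so the true figure is lower, but the article gives no correlation between them. For unadjusted tests over all 14 parameters, with visit correlation 0.5 and an assumed between-parameter correlation from 0.9 to 0, simulation gives about 33–86% over three visits and 39–91% over four.

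**The case against.** **The sentence itself inflates nothing.** Applied as written, to two groups within one altitude, LSD is redundant and mislabelled. The multiplicity across visits and parameters would exist whatever method was named. This stands. It is why the point is the false description together with the absence of any stated control, and not harm caused by LSD.

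**A gate may be intended.** The treatment-by-altitude interaction is a natural overall test to precede LSD. If it were used as a gate, simulation puts the false-positive rate at about 1–3% when there is no effect anywhere. A full protocol or SAP may say so, and for that reason I say only that this article states no gate. Even a gated LSD leaves the individual p-values unadjusted, so calling them adjusted would still be wrong.

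**The family may be small.** The hypothesis in section 2.1 concerns acclimatization and de-acclimatization, and the limitations paragraph describes follow-up as days 17 and 28. Day 11 precedes ascent, and the 6-month visit comes long after dosing ends. This is a fair reading, so the two-visit figures are included. Against it, section 2.5 puts all four visits under the primary outcome, and day 11 is already on treatment because section 2.6 places those tests in the last three of the 14 days of medication. If success required a difference at both day 17 and day 28, no adjustment between them would be needed, but no such rule is stated.

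**The authors call the results preliminary and name LSD openly.** Both are true, and they limit the consequences. They do not make the sentence correct.

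**A stronger reading to avoid.** A reader might infer that LSD will also be used for visit-by-visit comparisons within each arm. That would give about 12–21% per arm and 23–38% over both arms (three or four visits, correlation 0.5), and so up to four times the nominal level or more. Section 2.11.2 does not announce such comparisons: it speaks of within-altitude differences between the two groups. Those figures should not be charged to the plan.

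**Conclusion.** The description of LSD as an adjustment is wrong as written. With one contrast per altitude and no stated gate, the p-values are nominal. For one variable, the between-group contrasts carry a false-positive rate of about 8–9% over two visits, 10–13% over three and 12–16% over four, or roughly 1.5 to 3 times 5%. These figures assume no true effect at any visit, normal data, 20 and 21 participants, no gating, and visit correlation between 0.8 (assumed) and 0.5 (the plan's value). The rate over all 14 parameters is higher, but its size depends on correlations the article does not give, so I attach no single figure to it.

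**What to change.** In section 2.11.2, replace LSD with Holm's sequential Bonferroni procedure over the between-group contrasts at the planned visits, and list those visits. With two visits, for example, the smaller p-value is compared with 0.025 and, if it passes, the larger with 0.05.

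Holm over visits for each variable does not cover the 14 parameters. So also name one CPET variable as primary, and label the per-altitude comparisons of the others as unadjusted and descriptive. Table 5 and the Discussion already call peak VO2 or VO2max the gold standard, which makes it the obvious candidate.

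The minimum acceptable change is to stop describing LSD as an adjustment and to report those p-values as unadjusted. If a gated LSD is intended, name the gate and still do not call the p-values adjusted.

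Settle this before the allocation is opened, which section 2.4.1 places at the end of the statistical analysis unless an adverse event occurs. The cost is one or two sentences, no new data, and slightly larger p-values for some contrasts. The loss of power cannot be quantified because the effect size behind the sample size is not stated.
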